### Baseline assessment and follow-up measurements

The patient characteristics age, weight, height, gender, daily work, highest education, civil status, and preoperative physical therapy guidance (outside trial context) are prospectively recorded by means of a standardized interview during the baseline assessment. Data obtained from the patients’ medical records include history of COPD, smoking, pneumonia, diabetes mellitus, productive cough and cardiac events, tumor location, neoadjuvant treatment, prophylactic antibiotics, American Society of Anesthesiologists (ASA) score, admission and discharges dates, operation technique.

To evaluate the effect of IMT on respiratory muscle function and lung function, participants undergo measurements at five time points (baseline (T0), the day before surgery (T1), and during hospital stay on postoperative day 3 (T2), day 6 (T3), and day 9 (T4)). To determine an effect of IMT on quality of life (QoL) the EuroQol-5D and the SF-12 are assessed at baseline and 4 weeks after surgery. See for detailed description the paragraph secondary endpoints.

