### Sample size calculation

Sample size is calculated based on an expected reduction of 50% on the incidence of postoperative pneumonia [13]. Assuming a 30% incidence of postoperative pneumonia after esophageal resection in the control arm and using a significance level of 0.05 and a power of 80%, 118 patients are required in each arm [2,15,23]. Taking into account a 5% in-hospital mortality rate after surgery, approximately 124 patients per arm need to be included (248 patients in total).

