### Statistical analyses

Data analyses will be performed in accordance with the intention to treat principle. IBM SPSS statistics software (version 20 or higher) will be used for data analyses. A two-sided *P* value of less than 0.05 is regarded to be statistically significant. Analyses will be adjusted for center.

Literature shows that the odds ratio (OR) can be interpreted as relative risk (RR) when the incidence of the outcome is < 10%. When the incidence is high, the OR can overestimate the RR [24-26]. Therefore, analyses of dichotomous variables will be performed using logistic regression analysis when the incidence is ≤ 10% and with Log-binomial regression analysis in the case of an incidence of > 10%. The incidence of pneumonia will be compared between the two groups and results will be presented as OR or RR with a 95% confidence interval (CI). The risk difference and numbers needed to treat will also be calculated when significant differences are found between groups.

For the continuous secondary outcome measures duration of mechanical ventilation and length of stay (ICU and total), survival analysis (Cox proportional hazards regression model) will be used to determine differences in time to extubation and discharge. For the categorical secondary outcome measures other pulmonary complications and in-hospital mortality the OR or RR will be calculated. Other outcomes (for example, lung function, respiratory muscle function, quality of life) will be compared between groups using linear regression for parametric data or the Mann–Whitney U Test for non-parametric data. To determine differences between time points in lung function and respiratory muscle function, results will be analyzed using the repeated measurements method (General Linear Modeling Repeated Measures). In case of missing measurements or covariates, multiple imputations will be performed.

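### The Mann–Whitney fallback for the continuous secondary outcomes cannot carry the promised centre adjustment, and no baseline term is named for comparing the arms

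*Protocol article*

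**What the plan says.** All statements are in the Protocol article.

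- Statistical analyses sets a rule with no exception: "Analyses will be adjusted for center". Centre is the only adjustment variable it names.
- The same section says that outcomes such as lung function, respiratory muscle function and quality of life "will be compared between groups using linear regression for parametric data or the Mann–Whitney U Test for non-parametric data".
- It then plans a General Linear Model for repeated measures on lung and respiratory muscle function. The stated purpose is to find differences between time points. Quality of life is not included.
- Covariates are mentioned once more, without being named, in the sentence on multiple imputation.
- Secondary endpoints schedules FEV1, FVC, Pi_max and Pi_end at T0, the day before surgery, and postoperative days 3, 6 and 9. For quality of life, Baseline assessment and follow-up measurements says that "the EuroQol-5D and the SF-12 are assessed at baseline and 4 weeks after surgery".
- Study design and setting stratifies randomisation by centre and minimises on surgical technique. Recruitment and informed consent lists eight hospitals in three countries.

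**The concern.** There are two linked problems.

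The first is an inconsistency within one section. If an outcome is judged non-parametric, the named test cannot adjust for centre, although centre is a stratification factor and the Discussion describes usual care as differing in every centre. Whether an arm comparison is centre-adjusted then depends on a distribution seen only after the data are in. The branch may well be used: Pi_end is limited to between 3 and 7 minutes at baseline, and a bounded measure is a natural candidate for it.

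The second is that every one of these outcomes has its own baseline value, and the text gives that value no stated role in the between-arm comparison. The Discussion relies on the respiratory measurements to show whether the training effect is still present after surgery and to explore the mechanism. Less precise estimates, or estimates carrying a chance difference at T0, would weaken that part of the trial.

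**Working it through.** **1. The plan's own figure.** The article gives no calculation for the continuous outcomes, so the only figure to reproduce is the primary sample size. Inputs from Sample size calculation: control incidence 30%, halved to 15% ("Sample size is calculated based on an expected reduction of 50% on the incidence of postoperative pneumonia"), significance level 0.05 (two-sided, from Statistical analyses), power 80%.

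n per arm = (1.960 + 0.842)² × (0.30 × 0.70 + 0.15 × 0.85) / 0.15² = 7.849 × 0.3375 / 0.0225 = 117.7, so 118.

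This matches the plan; the pooled-variance formula gives 121. The mortality allowance gives 118 / 0.95 = 124.2, consistent with about 124. The figure stands, and 118 per arm is used below as the number analysed.

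**2. The text set side by side.**

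| Outcome | Regression branch | Mann–Whitney branch | Other stated route for T0 |
|---|---|---|---|
| FEV1, FVC, Pi_max, Pi_end | Centre by the general rule; baseline neither named nor excluded | Neither centre nor baseline possible | Repeated-measures model, stated for time differences |
| EuroQol-5D, SF-12 | Same | Neither centre nor baseline possible | None |

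**3. What a baseline term is worth.** The article gives no standard deviation (SD) and no baseline to follow-up correlation r, so r is assumed over a range. Adding the baseline value multiplies residual variance by 1 − r². As a reference, take the difference that has 80% power without baseline at 118 per arm: d = √(2/118) × (1.960 + 0.842) = 0.365 SD. Power with baseline is Φ(2.802/√(1 − r²) − 1.960). The n per arm for 80% power is 118 × (1 − r²), rounded up.

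| Assumed r | Variance factor 1 − r² | CI width factor √(1 − r²) | Equivalent sample size 1/(1 − r²) | Power at 0.365 SD | n per arm for 80% |
|---|---|---|---|---|---|
| 0.3 | 0.91 | 0.95 | 1.10 | 84% | 108 |
| 0.5 | 0.75 | 0.87 | 1.33 | 90% | 89 |
| 0.7 | 0.51 | 0.71 | 1.96 | 97.5% | 61 |
| 0.8 | 0.36 | 0.60 | 2.78 | 99.7% | 43 |

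**4. Chance imbalance.** The standard error of the baseline difference between arms is √(2/118) = 0.13 SD, so an imbalance of 0.2 SD is about 1.5 standard errors. It would shift an unadjusted difference by r × 0.2: 0.10 SD at r = 0.5 and 0.14 SD at r = 0.7. These are 27% and 38% of the 0.365 SD reference.

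**5. What losing centre costs.** Simulation with 3,000 runs per setting, 236 patients, eight centres, arms balanced within centre, true difference 0.365 SD and r = 0.5. The between-centre SD is assumed.

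| Between-centre SD (in within-centre SDs) | Mann–Whitney | Regression with centre | Regression with centre and baseline |
|---|---|---|---|
| 0 | 77% | 78% | 88% |
| 0.5 | 71% | 80% | 90% |

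The simulated outcomes are normal. The table therefore shows what is lost by dropping centre and baseline, not how the methods rank on skewed data. Simulation error is about 0.7 percentage points (√(0.8 × 0.2/3,000) = 0.007).

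**The case against.** The strongest objection is that silence is not a decision. Linear regression can carry a baseline term, covariates are mentioned without being listed, and a condensed article may leave the list to a fuller plan. That stands. A reader might infer that the trial will compare raw follow-up values, but the article neither names nor excludes baseline, so that reading is not supported.

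The repeated-measures model also deserves weight. T0 is one of its five time points, and with arm as a factor its time-by-arm term would use T0. This may serve lung and muscle function. However, the article states the model for differences over time and not for the arm contrast, and it does not cover quality of life.

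The gain is conditional too. No correlation is documented, one value need not fit both the day before surgery and the days after a major resection, and at r = 0.3 the gain is small. A bounded Pi_end may be a weaker baseline covariate, and neither a log scale nor robust standard errors resolve bounding. A Hodges–Lehmann shift can accompany a Mann–Whitney test, so the lack of an effect in measurement units is not inherent to that test.

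None of this removes the conflict between the centre rule and a test that takes no covariates. A fuller covariate list could not repair that branch while the plain test remains in it.

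**Conclusion.** The point holds in a limited form. The Mann–Whitney branch contradicts the centre-adjustment rule in the same section, and it makes the adjustment depend on the observed distribution. Separately, baseline values are collected for all these outcomes but given no stated role in the arm comparison; the gap is clearest for quality of life.

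On the assumed correlations of 0.3 to 0.8, a baseline term would cut residual variance by 9% to 64% and narrow confidence intervals by about 5% to 40%. Dropping centre cost about 9 power points in the simulation with an assumed between-centre SD of 0.5, and only 1 to 2 points with no centre effect.

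A reader might also infer that the treatment estimates would be biased. Randomisation rules that out on average: the cost is precision, plus whatever imbalance happens to occur at T0. Only secondary outcomes are affected. The pneumonia analysis and the 248 patients are untouched.

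**What to change.** State one between-arm model for each continuous outcome in this group: linear regression of the follow-up value on arm, the outcome's own T0 value and centre. Surgical technique, the minimisation factor, may be added. If the repeated-measures model is meant to supply the arm contrast for lung and muscle function, say so and state how T0 enters it.

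Replace the plain Mann–Whitney fallback with a method that keeps the same covariates, chosen per outcome in advance where possible: transformation, robust or bootstrap standard errors, rank-based ANCOVA or a proportional-odds model. For a bounded measure such as Pi_end, the last two are the more natural candidates. A van Elteren test stratified by centre would restore centre but not baseline.

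The cost is analysis wording only. All baseline values are already collected, and no patient, visit or measurement is added.

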### Study population

All patients diagnosed with esophageal cancer and scheduled for esophageal resection with gastric conduit reconstruction by either a transhiatal esophageal resection (THE), a transthoracic esophageal resection (TTE), or minimally invasive (robot-assisted or conventional) thoraco-laparoscopic esophageal resection (MIE) are considered eligible for inclusion.

Further inclusion criteria are: (1) the patient is (cognitively) capable to understand and perform a preoperative IMT program; (2) the operation is scheduled at least 2 weeks after signing informed consent, since the patients need to be able to follow the intervention program for at least 2 weeks; and (3) the patient is willing to sign the informed consent form.

Patient are excluded based on the following criteria: (1) the patient is unable to communicate in the Dutch language; (2) age <18 years; and (3) the patient is participating in a conflicting trial concerning esophageal resection.

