### Recruitment and informed consent

Patients are recruited from eight esophageal resection hospitals (in The Netherlands: Atrium Medical Center Heerlen, Canisius Wilhelmina Hospital Nijmegen, Reinier de Graaf Group Delft, University Medical Center Utrecht, VU Medical Center Amsterdam, Hospital Group Twente Almelo; in Belgium: University Hospital Gasthuisberg Leuven; and in Ireland: St. James’s Hospital Dublin). In every participating center one oncological surgeon and one physical therapist (PT) are the contact people for the coordinating researcher. Inclusion takes place for a period of approximately 1 year (September 2013 to August 2014). The local oncological surgeon determines whether a patient is eligible for inclusion in the PREPARE trial based on the inclusion criteria. At the start of the chemoradiation period or at the time the patient is informed about the planned surgery (when chemoradiation is not indicated), the surgeon informs the patient about the trial and hands over the trial information letter. After at least 5 days the patient is contacted by phone. When the patient is motivated to participate, an appointment with the local assessor is scheduled (after the chemoradiation period) for signing the informed consent form and completing the baseline measurements. The baseline measurement is followed by randomization, and the IMT instruction for patients in the intervention group. Both performed by the involved PT.

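### The unrestricted multiple-imputation rule, read literally, fills in postoperative values for patients who died or were never resected, and the repeated-measures analysis leans on it without giving the arm difference at each visit

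*Protocol article*

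**What the plan says.** All references are to the protocol article.

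- **Missing data** (Statistical analyses): "In case of missing measurements or covariates, multiple imputations will be performed". No exception follows.
- **Population** (Statistical analyses): "Data analyses will be performed in accordance with the intention to treat principle".
- **Timing of randomization** (Recruitment and informed consent): "The baseline measurement is followed by randomization, and the IMT instruction for patients in the intervention group". Under Study population, "the operation is scheduled at least 2 weeks after signing informed consent". Some weeks therefore pass between randomization and surgery.
- **Visits** (Baseline assessment and follow-up measurements): lung and respiratory muscle function are measured at baseline (T0), on the day before surgery (T1), and "during hospital stay on postoperative day 3 (T2), day 6 (T3), and day 9 (T4"). Quality of life is measured at baseline and 4 weeks after surgery.
- **Between-arm analysis** (Statistical analyses): lung function, respiratory muscle function and quality of life "will be compared between groups using linear regression for parametric data or the Mann–Whitney U Test for non-parametric data". A general statement adds adjustment for centre.
- **Analysis over time** (Statistical analyses): "To determine differences between time points in lung function and respiratory muscle function, results will be analyzed using the repeated measurements method", specified as General Linear Modeling Repeated Measures.
- **Purpose** (Study objectives; Discussion): postoperative respiratory muscle and lung function are secondary objectives. The Discussion expects these measurements to show whether the effect of training persists after the operation.

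**The concern.** A lung function test that a living, operated patient did not perform is a missing value. A 4-week quality-of-life score for a patient who died in the first week is not: there is no such value. The same holds for a postoperative day 3 measurement in a patient who was never operated on. The imputation sentence draws no such line, and intention to treat with randomization before surgery brings both kinds of patient into the analysis set.

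Imputed scores for the dead would resemble those of survivors. If deaths differ between arms, this favours the arm with more deaths and hides part of any benefit.

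The repeated-measures analysis adds to the problem. In its classical form it uses only patients with every visit complete, so patients with a gap enter only through imputation. Its stated target, differences between time points, would largely show the course of lung function around surgery. Whether training still makes a difference at days 3, 6 and 9 is a question about arm at a given time. Neither analysis sentence says how that will be estimated.

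**Working it through.** **1. The plan's own figure.** For 30% versus 15% pneumonia, two-sided alpha 0.05 and 80% power, the unpooled normal formula gives 117.7, that is 118 per arm. Allowing for 5% mortality, 118 / 0.95 = 124.2, in line with the stated 124 per arm and 248 in total. The sample size reproduces and is not in dispute. It matters here because it shows that deaths are expected.

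**2. Deaths.** 0.05 × 248 = 12.4, about 12 patients or 6 per arm. This is in-hospital mortality, so it only approximates deaths before week 4. For T2 to T4 only visits after the death are affected, so 12 is an upper figure there.

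**3. Could deaths differ by arm?** The Background gives 20% mortality with pneumonia and 3% without. Assume that this relation is causal and that the full 50% reduction occurs:

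- control: 0.30 × 0.20 + 0.70 × 0.03 = 0.081, or 10.0 of 124
- training: 0.15 × 0.20 + 0.85 × 0.03 = 0.0555, or 6.9 of 124

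Both rates exceed the 5% used for planning, so this is an illustration and not a forecast.

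**4. Patients never resected.** The article gives no rate. With an assumed rate q, and 5% mortality among the rest, the number affected is 248q + 0.05 × 248(1 − q):

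| Assumed q | Never resected | Deaths | Affected | Share of 248 |
|---|---|---|---|---|
| 0% | 0 | 12.4 | 12.4 | 5.0% |
| 2% | 5.0 | 12.2 | 17.1 | 6.9% |
| 5% | 12.4 | 11.8 | 24.2 | 9.8% |
| 10% | 24.8 | 11.2 | 36.0 | 14.5% |

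**5. Possible effect on quality of life.** Assume a survivor EuroQol-5D mean of 0.75 and, for scale only, a score of 0 for death. The arm difference hidden by survivor-like imputation is 0.75 × (0.081 − 0.0555) = 0.019. With an assumed SD of 0.20 to 0.25 and 124 per arm, the standard error of the arm difference is SD × √(2/124) = 0.025 to 0.032. The shift is below one standard error.

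**6. Dependence of repeated measures on complete visits.** Assume that T0 is complete and that 10% or 20% are missing at each of T1 to T4.

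- Missing independently: 0.90⁴ = 66% or 0.80⁴ = 41% have all five visits.
- Fully nested (the same patients miss every visit): 90% or 80%.

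Postoperative visits end with discharge or death, so losses will tend to be nested and the truth should lie between these limits.

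**7. The two analysis sentences side by side.** The between-arm sentence covers lung function, respiratory muscle function and quality of life, but names neither a visit nor the baseline value. The repeated-measures sentence covers lung and respiratory muscle function only and names time but not arm. The arm difference at each postoperative visit, adjusted for baseline, is fixed by neither.

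**The case against.** **Arms are compared.** A reader might infer from the repeated-measures sentence that the plan tests change over time instead of comparing arms. The text does not support that. The sentence before it compares the arms, and repeated measures is an addition. Nor is repeated measures planned for quality of life. Both objections stand in full.

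**The rule may not reach the dead.** The text speaks of missing measurements, and a value that cannot exist is arguably not missing. Enlarging the sample for mortality also suggests that deaths are regarded as lost data. The full protocol or analysis plan, not shown, may limit the rule. So it cannot be said that the trial will impute for the dead, only that the sentence as written permits it. The point still survives: the article is not silent but states a rule that is too broad.

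**The size is uncertain.** The 0.019 needs an assumed mean, a causal reading of the mortality figures, and death scored as 0, which the protocol does not adopt. The 66% and 41% are the pessimistic end. This stands.

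**The mixed model has a related weakness.** A likelihood-based model of all observed values assumes missing at random and implicitly extrapolates beyond death. This also stands, and the results must be labelled accordingly.

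**Only secondary outcomes are involved**, and the Discussion describes the analyses of mechanism as exploratory. That is correct and limits the weight of the point. However, postoperative respiratory muscle and lung function are themselves listed as secondary objectives.

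**Conclusion.** The point holds in a limited form. One unrestricted imputation rule, combined with intention to treat and randomization before surgery, literally covers postoperative values that do not exist. The protocol's own mortality figure makes this about 12 of 248 patients. Under assumed non-resection rates of 2% to 10% it becomes about 17 to 36.

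The supplementary repeated-measures analysis relies on that imputation for every patient with a gap. The arm difference at each postoperative visit, which the Discussion's question calls for, is not specified.

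The likely numerical effect on quality of life is small: about 0.02 on EuroQol-5D under the assumptions shown, and less than one standard error. Its direction would be systematic if deaths differ by arm. Nothing here bears on the pneumonia endpoint or the sample size. It is a correction worth making before the data are unblinded, not a threat to the trial's main conclusion.

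**What to change.** 1. Restrict multiple imputation to measurements that could exist: the patient is alive at the visit and, for postoperative measures, has been resected. Keep it for covariates and for living patients with missed measurements.
2. Report 4-week quality of life in survivors, labelled as conditional on survival, with deaths by arm beside it. Scoring EuroQol-5D as 0 for death is a choice of estimand and belongs at most in a sensitivity analysis.
3. State how patients who were never resected enter the postoperative secondary outcomes, and report their number by arm.
4. Replace GLM repeated measures with a linear mixed model of the observed T1 to T4 values. Include the T0 value, centre, surgical technique, arm, time and arm-by-time, and report the arm difference with confidence interval at each visit.

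**Cost.** The change is to analysis wording only. SPSS, the named software, fits mixed models, and no new data or patients are needed. Two limits remain. The survivor-only comparison is no longer a comparison of all randomized patients. The mixed model still assumes missing at random for living patients and extrapolates implicitly after death. Both should be stated with the results.
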